## Methods

### Study design

A mixed methods research design will be used to evaluate this intervention. Specifically, we will a). conduct a formative implementation evaluation using rapid qualitative methods, and b) assess the programmes effectiveness via an interrupted time series analysis looking at patient centered outcomes using routinely collected electronic health records.

### Ethics approval and consent to participate

No data collection is required for quantitative analyses. Secondary analyses will be conducted on HES datasets. Ethical approval was obtained for the qualitative study as follows:

For the component covering national and regional staff interviews: University College London Research Ethics Committee ID 26505/001.For the component covering staff based within NHS sites and patients: approved by the HRA and Health and Care Research Wales (HCRW), reference number: 24/NE/0109.

### Qualitative methodology: Implementation evaluation

This is to be a formative implementation evaluation of the programme as implemented nationally, across the NHS in England. It will use qualitative methods, including interviews with staff, patients and carers, meeting observations, and documentary analysis. The evaluation will be guided by the revised Consolidated Framework for Implementation Research (CFIR) [16] and the NICE patient experience framework [17]. CFIR is designed to aid understanding of factors influencing implementation and was recently extended to incorporate different types of outcome [16]. The NICE patient experience framework provides 5 standards to guide quality of care improvement.

### Qualitative methodology: Study timeline

Months 1–2 – Implementation evaluation; gaining ethical and local research governance permissions.Months 3–13 – Implementation evaluation; recruitment, data collection and analysis will run in parallel. Interim findings disseminated.Month 14 – Implementation evaluation; final write-up of results and submission of outputs.

Participant recruitment for the implementation evaluation across all study sites is expected to begin on 1 March 2025 and is expected to be completed, along with data collection, by month 13.

### Qualitative methodology: Sampling

This implementation evaluation will be coproduced with academic researchers, national leadership, local services, and patient and carer representatives. It will employ rapid qualitative methods to enable ongoing dissemination of formative learning with participating national and local stakeholders. It will use a multiple-case study design. Case studies permit in-depth analysis of change and its implications within specific contexts, while cross-case comparison (i.e., comparison across multiple case sites) permits identification of both context-specific and cross-cutting lessons on implementation and impact.

To optimise learning, we will sample case sites purposively at organisational and service levels (Table 1) in a range of organisation types (e.g., NHS Foundation Trusts, Teaching Hospitals, District General hospitals), serving different populations in different settings (e.g., large urban area, more rural or mixed geographies). We will study implementation in three contrasting surgical ‘tracer conditions’, varying in terms of urgency/types of options available to patient and clinicians: [1] colorectal cancer surgery (a relatively common and potentially life-threatening surgical condition), [2] repair of abdominal aortic aneurism (prophylactic surgery to address significant risk), and [3] primary knee replacement (elective, non-urgent surgery to address long-term quality of life). Finally, we will sample services at different stages of implementation/uptake, to ensure that we can identify lessons both on common challenges and how services engage with these to progress implementation. NHSE England have provided us with a list of sites (who have consented to be contacted) and an indication of the degree of implementation across the different specialties. Degree of implementation will be one of the variables we consider (in addition to geographical region, type of hospital, etc.) to select the sites included in the study. This variation will help reduce the risk of bias in our sampling.

**Table 1 pone.0335129.t001:** Overview of sampling for service-level case studies.

Dimension	Characteristic	Examples
Organisational	Status	Secondary/tertiary referral centers Unit performs surgery only on local patients
	Population served/ Demographics	Age Gender Ethnicity Socioeconomic status
	Setting	Urban Rural/mixed
Tracer services	Urgency/nature of condition and surgical process	Colorectal cancer surgery: treating potentially deadly disease. Repair of abdominal aortic aneurism: prophylactic surgery to reduce likelihood of potentially fatal rupture. Knee replacement: elective, non-urgent surgery to address pain and enable physical wellbeing.
Implementation	Status/stage of progress	Substantial progress/uptake Limited progress/specific obstacles

Within cases, we will collect qualitative data from a range of sources to optimise our analysis of implementation, uptake, and outcome (Tables 2 and 3). We will interview stakeholders with different perspectives on new services, including people involved with organisation and delivery of early screening and optimisation and associated surgical care, service management and system oversight, and national programme leadership (Table 2). We will conduct non-participant observations of governance meetings (at service, region, and national level) related to safe and effective delivery of early perioperative screening and optimisation (Table 3). Finally, we will collect relevant documents, including project plans, service protocols, meeting minutes, service reviews, and information transfer/sharing policies to understand ongoing development of and decision-making around services. Data will be collected from 5 sites using the sampling framework outlined in Table 2. It is possible there will be a limited number of people with relevant experience of the new programme. Therefore, interviews will be completed once we either reach saturation, defined by no new data presenting in the interviews [18], or where all relevant participants have been approached.

**Table 2 pone.0335129.t002:** Overview of anticipated interviewees (NB numbers are ‘up to’/maximum).

	Total across all 5 sites
** *Stakeholder group* **	
Patients	25 (5 at each site)
Preoperative assessment teams	10 (2 at each site)
Surgical teams	15 (3 at each site)
Managers and administrators (team/hospital)	10 (2 at each site)
Regional context (e.g. primary/social care, ICS, charities)	20 (across the national/regional workforce)
** *Total* **	70

**Table 3 pone.0335129.t003:** Overview of anticipated non-participant observations (NB numbers are ‘up to’/maximum).

	Total across all 5 sites
** *Activity* **	
Oversight meetings - national	**4**
Oversight meetings - regional	**10**
Oversight meetings - service	**10**
*Total*	**24**

## Participants will be screened following the below inclusion and exclusion criteria

### Qualitative methodology: Inclusion criteria

Patients/carers – Interviews will be conducted with participants who:

Have been offered surgery for one of the three tracer conditions in this study (colorectal cancer, abdominal aortic aneurysm, knee osteoarthritis – primary knee replacement), or care for someone who has been offered surgery for one of the three tracer conditions.Are aged 18 or over.Have capacity to consent to participation.Carers who are decision makers and wish to take part on behalf of the patients.Carers where the patient would like somebody present with them in the interview.

### Staff – Interviews and observations

Working in the participating case sites and clinical settings.Preoperative assessment team members, including nurses and other non-medical professionals. Key roles will include nursing/non-medical lead; medical lead (usually an anaesthetist) and other medical preoperative assessment staff members. If applicable, non-registered healthcare workers (e.g., perioperative care coordinators; digital health assistants; healthcare assistants).Surgical teams (to include at least one surgeon, one surgical administrator, and one member of a booking and scheduling team).Managers (e.g., of team, division, and hospital).Wider context (e.g., regional system leaders, commissioners, patient representative groups).• National programme leadership.

### Qualitative methodology: Exclusion criteria

All participants will be excluded if they are under 18 years of age or lack capacity to consent. Staff participants will be excluded if they have not been involved in organisation or delivery of the early perioperative screening and optimisation programme.

## Qualitative methodology: Recruitment

### Interviews

Potential staff interviewees will be identified through a combination of local documentation, identification by local stakeholders and engagement activities. Researchers will approach potential staff participants initially by sharing study information by email. Patient participants will be identified by local staff or research delivery teams. Patients who have accessed the clinical service under the new guidance may be approached in clinic, by email or phone. This might mean that local staff will share a copy of the PIS. Local staff or research delivery teams will gain written or verbal consent to pass on patient contact details in line with local R&D requirements. UCL researchers will then approach potential patient participants in line with the above sampling approach and inclusion and exclusion criteria. In line with good practice and UCL requirements, recruitment documentation (i.e., information and consent forms) will make clear the anticipated burden and risks of participating and emphasise the voluntary nature of participation. Should any participants find the interviews distressing as they recall uncomfortable events, we will offer appropriate support by referring participants to local or national wellbeing services, including General Practitioner (GP) services and they will be reminded that they can stop the interview at any time. All potential participants will be given at least 48 hours to decide whether they would like to take part in the interview. They will be asked to complete a consent form (written or electronic) and return it to the research team in advance of the interview and a mutually convenient time and platform (telephone or MS Teams) will be agreed upon.

### Non-participant observations

Key meetings for observation will be identified through a combination of local documentation, and identification by local stakeholders. Participant information sheets will be circulated with meeting papers to all attendees in advance of the meeting. Verbal agreement for the observation to take place will be requested from those taking part in the meeting and agreement will be documented in the minutes; confirmation of ongoing agreement to be observed will be obtained at the beginning of each event that is to be observed and recorded in the meeting minutes and observation fieldnotes.

## Qualitative methodology: Data collection

### Interviews

Staff and patient/carer interviews will be guided by semi-structured topic guides (see S1 File–S3 File. These will be co-developed with clinical and patient representatives and guided by our research questions. Participants will take part in a single interview lasting 30–60 minutes which will be recorded on MS Teams or digital recorders. During each interview, the researchers will take notes, and a summary of these notes will be added to the RREAL Sheet. We will collect the ethnicity of the participants to assess the diversity of respondents.

### Non-participant observations

Observations of key meetings will be conducted online. They will be guided by observation templates reflecting our research questions, e.g., exploring how these services are led and overseen, monitoring of uptake and impact of services, how decisions are made around emerging problems and opportunities to improve quality. Observations will be recorded as field notes collected by the researchers and saved on the secure UCL drive.

### Document review

Finally, Key documents will be either be in the public domain or will be documents not considered sensitive and will be shared with us by representatives of local services and the national programme.

### Qualitative methodology: Patient and public involvement

Two PPIE members have been recruited to join the implementation evaluation component of the study and are to be embedded throughout the full project lifecycle. Initial consultation with the PPIE members included a discussion of an outline of the study; its aims and objectives, and timelines, as well as a discussion around the proposed PPIE plan and if there were any training that the PPIE members felt they would benefit from to contribute to this study. PPIE members were given the opportunity to ask questions about the study and to contribute to the PPIE plan to ensure the activities were both reasonable and within their time capacity. PPIE members were remunerated following NIHR PPIE payment guidance [19]. Once a draft was finalised, the two members reviewed and provided feedback on this protocol, the participant information sheet, consent form and topic guides. In response to their feedback, we made amendments to the draft documents and provided responses to their feedback with what changes had or had not been made and why. Broadly, the study design was favourable with our PPIE members. However, one of the key changes we made to our protocol, following their feedback, was to restructure our aims and objectives so that they were easier to follow. We also discussed the importance and influence of the carer role in the patient pathway.

Throughout the study, PPIE members will be actively involved in discussions of our research approach and emerging findings; they will also contribute to discussions of the final analysis and implications of the research. In particular, these discussions will consider implications of the work for equality and diversity. If willing, the PPIE members will also be supported in contributing to dissemination activities, e.g., as co-authors of articles and summaries of findings, and speakers when presenting findings. PPIE members will be central to ensuring these outputs are presented in clear, accessible language, and that the lessons are relevant to patients and the public.

### Qualitative methodology: Data analysis

Data collection and analysis will be carried out in parallel and facilitated through the use of RREAL Sheets [20]. RREAL sheets will be developed per site (one for staff and one for patients) and used to facilitate cross-case comparisons and per population (to make comparisons between sub-groups). The RREAL sheets will then be used to summarise and share emerging findings on an ongoing basis [12]. Interview transcripts will be analysed using framework analysis; transcripts will be read for familiarisation; the research team will then label data considered relevant to the research questions (‘coding’). The codes will be grouped into categories to help form the final themes [21]. The framework will be informed by our initial research questions and topic guides, the main findings identified in the RREAL sheets and topics emerging from the data. The framework analysis for staff data will also be guided by the Consolidated Framework for Implementation Research (CFIR) [16] and the framework analysis for the patient data will be guided by the NICE patient experience framework [9]. The document review will facilitate the production of a programme theory to aid with our understanding of how the program is intended to work.

### Quantitative methodology: Effectiveness evaluation

### Data sources

For the effectiveness evaluation, we will use a cohort study research design using Hospital Episodes Statistics (HES) data. A bespoke dataset extracted from Hospital Episodes Statistics Admitted Patient Care (HES-APC), Critical Care (HES-CC) and HES linked Office for National Statistics (ONS) mortality data will be used to conduct this analysis.

HES is a high quality national secondary care database that reports all NHS hospital admissions in England. It includes detailed information on hospital activities including admission dates, diagnoses and procedures, duration of stay and patient demographic information [22]. The access to the data is managed by NHS Digital. Relevant data fields used in this research are detailed in S4 File.

### Quantitative data management

The effectiveness analysis will be conducted on pseudonymised data. Data linkage and extraction will be conducted by NHS Digital and once completed data will be held in a secure data system at UCL that meets ISO27001 certification [23]. All analyses will be conducted within the secure data system by appropriately trained researchers.

### Quantitative methodology: Study timeline

The expected start date for this aspect of the study will be 15 January 2026.

Months 0–9 – Effectiveness evaluation; submit HES data access application, work to gain access to the linked dataset. While waiting for the data access, we will revise our statistical analysis plan.Months 10–12 – Effectiveness evaluation; data cleaning and exploratory data analysis. Interim findings disseminated via internal reports and presentations.Months 13–18 – Effectiveness evaluation; finalise statistical analysis, write-up and submission of outputs.

### Quantitative methodology: Primary outcome

The primary outcome of the quantitative study component is days alive and out of hospital (DAOH) at 30 days after surgery. This patient-centred outcome measure has been clinically validated internationally and is related to clinically relevant patient characteristics, surgical complexity, in-hospital complications, and long-term outcomes [24–26]. We will also assess DAOH at 180 and 365 postoperative days to provide information on longer term mortality outcomes [27].

We will use similar methodology to construct DAOH as detailed elsewhere [27,28]. Specifically, to calculate DAOH of a defined period, we will subtract the total post-operative duration of initial and any next subsequent hospital stays from the total period length to obtain the numbers of days spent out of hospital. The time spent in a non-hospital care facility will not be accounted for in our analyses [27]. DAOH will be defined as 0 days if a patient died within the defined period. A longer DAOH will be indicative of more favourable outcome. For each DAOH at 30, 180 and 365 variable respectively, there will be a ceiling 30/180/365. DAOH data will be calculated based on event date of corresponding operation procedure ICD-10 code, length of stay data related to each hospital admission and subsequent re-admission, discharge date and discharge destination from HES APC dataset and death date from HES-ONS linked mortality dataset.

### Quantitative methodology: Secondary outcomes

The secondary outcomes of this study are postoperative length of stay in hospitals and emergency re-admission within 30 days, as these are related to patient safety in peri-operative setting [29]. Both variables will be constructed using extracted data fields in HES data. In addition, we will examine days spent in critical care [30]. Finally, we will consider related costs using Healthcare Resource Groups (HRG) codes in HES datasets and linking them to the National Tariff.

In addition, we plan to assess the impact of early preoperative screening on the incidence of short-term cancellations by linking data from the Theatre Productivity Dataset with Perioperative Care Census conducted by NHS England [31]. These datasets collect information at the hospital site level, and are currently in their infancy. Data quality and completion will be assessed prior to any analyses to ensure findings are reliable and robust.

### Quantitative methodology: Effectiveness statistical analysis

The study population is defined to align with the qualitative component of the study. That is, all adults undergoing colorectal cancer surgery, repair of abdominal aortic aneurism or knee replacement at an NHS hospital in England between Jan 1^st^ 2018 and April 1^st^ 2026 in HES APC dataset.

In the absence of randomisation, quasi-experimental research designs are increasingly used for evaluating population health interventions [32,33]. In this analysis, we will use an interrupted times series research design: this method has been widely used to evaluate health interventions with time series data [34].

HES provides a long time series dataset, and, without a control group, a single interrupted time series analysis is the most suitable design to evaluate the programme [35]. We will conduct segmented regression analysis on monthly DAOH measures, postoperative length of stay, rate of emergency re-admission in 30 days,days spent in critical care and also relevant costs [36].

Based on date of surgery, in this analysis we will model monthly data at different time periods between Jan 1st 2018 to Jan 1st 2026, with Jan 2018 to end of Feb 2023 data as baseline period. Intervention period is March 2023 to end of March 2024. Post-intervention period is April 2024 to April 2026.

Specifically, we will model the following:

$$Y_{t}=\;\beta_{\text{0}}+\beta_{\text{1}}T+\beta_{\text{2}}X_{\text{1}t}+\beta_{\text{3}}{(T-T_{i})X}_{\text{1}t}\;+\beta_{\text{4}}X_{\text{2}t}+\beta_{\text{5}}{(T-T_{d})X}_{\text{2}t}\;+\;\varepsilon_{t}$$

Where Yt is the outcome at time t, T represents the time since the start of the study, X_1t_ is a dummy (0/1) variable indicating the intervention period [1] or otherwise 0, X_2t_ is a dummy variable representing the post-intervention period, Ti represents the time point when the intervention starts (X_1t_=1 for T ≥ Ti). Td represents the time point when the post-intervention period starts (X_2t_=1 for T ≥ Td). [37]

$\beta_{\text{0}}$ represents the baseline level of Y at T=0

$\beta_{\text{1}}$ represents underlying pre-intervention trend

$\beta_{\text{2}}$ represents the intercept change immediately following the intervention

$\beta_{\text{3}}$ represents the change in the slope of the trend following the intervention

$\beta_{\text{4}}$ represents the intercept change immediately post the intervention

$\beta_{\text{5}}$ represents the change in the slope of the trend post the intervention

Details of this methodology are available elsewhere [37].

In our analysis, by stratification, we will examine variations in time trend patterns in geographic location and patients characteristics including age groups, gender, ethnicity and deprivation measured using Index of Multiple Deprivation quantiles. We will use region of residence and local integrated care board in HES data to indicate geographical locations. Age will be grouped as 18–44, 45–65, 66–79, and 80 plus [38]. Ethnicity will be grouped based on ONS 2021 census ethnic categories, including White, Asian and Asian British, Black and Black British, Mixed or multiple ethnic groups, and Other ethnic group. In addition, we will explore variations in NHS hospital sites.

We will also check for seasonality impacts through sensitivity analyses such as using time stratified model, periodic functions or flexible spline functions that are detailed elsewhere [39]. The timing of rollout of the intervention was likely to be different across hospitals, therefore, we will conduct a sensitivity analysis with different definitions of the intervention period (i.e., early implementation period- 1^st^ March to 31^st^ Aug 2023 vs late implementation period – 1^st^ Sep 2023–31^st^ March 2024). Given the dramatic impact of Covid on health services, we will also assess the impact of a shorter baseline period of between Jan 2018 to Feb 2020. In addition, concurrent national programmes that target similar outcomes, such as Getting it Right First Time (GIRFT) [40], could confound our results. We will conduct sensitivity analyses that will stratify by different time periods to adjust for relevant national programmes if there are well-documented dates of implementation and can be distinctly modelled within our time series. We will conduct complete case analyses. Stata 17 (StataCorp) and R 4.2.2 (R Core Team, 2022) will be used to conduct the analysis.

Finally, to examine short-term cancellation, we will conduct descriptive data analysis and describe short-term cancellation data across different time periods and geographical regions.

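### The quantitative cohort is said to match the qualitative tracers but is defined more broadly, and the emergency operations it admits dilute a calendar-time effect

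*Protocol article*

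**What the plan says.** The protocol article, under Quantitative methodology: Effectiveness statistical analysis, opens with the statement that "The study population is defined to align with the qualitative component of the study". The next sentence spells this out as "all adults undergoing colorectal cancer surgery, repair of abdominal aortic aneurism or knee replacement at an NHS hospital in England", for operations from January 2018 to April 2026. Nothing there refers to admission method, rupture status, or primary versus revision surgery.

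The qualitative component describes its tracers more narrowly:

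- **Knee.** Sampling: "primary knee replacement (elective, non-urgent surgery to address long-term quality of life". The Inclusion criteria list the conditions as "colorectal cancer, abdominal aortic aneurysm, knee osteoarthritis – primary knee replacement".
- **Aneurysm.** Sampling: "repair of abdominal aortic aneurism (prophylactic surgery to address significant risk". Table 1: "prophylactic surgery to reduce likelihood of potentially fatal rupture".
- **Colorectal.** Sampling: "colorectal cancer surgery (a relatively common and potentially life-threatening surgical condition", with no limit on urgency.

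Exposure in the segmented regression is set by month of surgery: baseline to February 2023, intervention period March 2023 to March 2024, post-intervention period from April 2024. The planned stratifiers are geography, age, gender, ethnicity and deprivation, with hospital site explored as well. The Discussion accepts that the programme cannot be tied to individual patients. The reasons it gives are uncertain rollout dates and services that already existed.

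**The concern.** The Introduction defines early screening as assessment earlier in the surgical pathway, and says that assessment close to surgery leaves little time to optimise health. A patient operated on during an emergency admission has no such interval. In the cohort as worded, that patient still counts as exposed if the operation falls after the programme began.

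Two things are at stake. First, operations that the programme cannot reach pull the estimated change towards zero. Second, if their share varies over time, the monthly mean of the primary outcome moves for reasons unrelated to the programme. DAOH makes this worse, because any death within the window scores 0 days.

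The mismatch also affects the integration of the two components. The Integrated approach section sets them side by side in joint displays and relates implementation maturity at five sites to patient outcomes, which works best when both describe the same patients.

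**Working it through.** The protocol states no effect size, power, or share of unplanned operations, so it has no figure to reproduce. The check is a comparison of texts, followed by arithmetic on labelled assumptions.

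**1. The two definitions side by side**

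| Tracer | Qualitative component | Quantitative cohort | Match |
|---|---|---|---|
| Knee | Primary and elective (Sampling); primary replacement for osteoarthritis (Inclusion criteria) | Any knee replacement | No |
| Aneurysm | Described as prophylactic (Sampling, Table 1); the Inclusion criteria name only the condition | Any repair | No, against the description |
| Colorectal | No limit on urgency | No limit on urgency | Yes |

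**2. Dilution**

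Let e be the share of operations done in emergency admissions (not in the protocol; assumed 5% to 20%) and Δ the programme effect in planned operations. Assume no effect in emergency operations and a stable e. Then

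pooled effect = (1 − e) × Δ + e × 0 = (1 − e)Δ.

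At equal standard deviation, the information needed rises by 1/(1 − e)². If a planned-only analysis had 80% power at two-sided 5% (a reference point, not a protocol figure), power at the same standard error would be Φ((1 − e)(1.960 + 0.842) − 1.960).

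| Assumed e | Effect retained | Information needed | Power |
|---|---|---|---|
| 5% | 0.95 | × 1.11 | 76% |
| 10% | 0.90 | × 1.23 | 71% |
| 20% | 0.80 | × 1.56 | 61% |

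Worked line for 20%: 0.80 × 2.802 − 1.960 = 0.28, and Φ(0.28) = 0.61.

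**3. Drift in case mix**

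Let g be the gap in mean 30-day DAOH between planned and emergency operations, and d the change in the emergency share. The monthly mean moves by d × g. For d = 0.02:

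- g = 5 days: 0.02 × 5 = 0.10 day
- g = 8 days: 0.02 × 8 = 0.16 day

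Both d and g are assumed.

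**4. Whether another planned analysis would catch it**

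None of the listed stratifiers is admission method, rupture status or primary/revision status. The shorter pre-COVID baseline changes which months are compared; it leaves emergency operations in every period. The case-mix monitoring in the Discussion names deprivation as its example, and monitoring does not change who is in the series.

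**The case against.** **A short label, not a definition.** The article uses plain knee replacement elsewhere for the same tracer (Abstract, Table 1), so the quantitative sentence could be read as carrying over the narrower definitions. That is possible, but the sentence is written as an explicit definition and takes in all adults undergoing the procedures. An analyst following it would apply no further filter.

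**Coding belongs to the full plan.** Code lists and filters are normally kept there, and the data fields are in S4 File, which is not shown. That would answer a complaint about missing detail. Here the cohort is stated, and stated more broadly than the claim that introduces it. S4 File is cited for data fields, not as a restriction of the population.

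**All-comers is a legitimate policy population.** It is, and dilution alone biases towards no effect. But the article does not present the broad cohort as that choice; it presents it as alignment.

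**The aneurysm mismatch is with a description.** This stands. Only the knee restriction appears in a formal inclusion criterion; prophylactic is how Sampling and Table 1 describe aneurysm repair.

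A reader might go further than the protocol allows in three ways:

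- That revision knees are also beyond the reach of screening. Nothing says so, and a revision can be a planned operation.
- That the colorectal cohort contradicts its tracer. Neither component restricts urgency, so only the dilution argument applies there.
- That emergency work continued while elective lists stopped, so the mix must have shifted. The article says only that COVID had a dramatic impact on services.

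**Conclusion.** The point holds as a contradiction between the stated alignment and the stated cohort, for knee replacement and for aneurysm repair as described. It has a statistical consequence for emergency operations in any of the three procedures: they are classed as exposed although they have no lead time for early screening.

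The direction of the dilution follows from assuming no programme effect in those operations. Its size cannot be derived from the protocol; the retained effect of 0.95 to 0.80 and the shift of 0.10 to 0.16 day illustrate assumed inputs only. Case-mix drift is a possibility that the analysis as described would not detect, not something the protocol shows to have happened. Revision knees count as a population mismatch and not as a source of dilution. The change is worth making because it is cheap and concerns the primary outcome.

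**What to change.** Preferred: define the primary analysis population as planned admissions, identified by HES admission method, for colorectal cancer surgery, unruptured abdominal aortic aneurysm repair and primary knee replacement. Keep the all-admissions series as a sensitivity analysis.

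Alternative: keep the broad cohort, remove the statement that it aligns with the qualitative component, and pre-specify a planned-only analysis beside it.

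Emergency operations could optionally serve as an internal comparison series, given that the Discussion lists the lack of a control group as its first limitation. This would need a stated assumption of no spillover, which is open to question because the programme also expands the perioperative workforce.

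The cost is a revised cohort sentence and a few filters on admission, diagnosis and procedure fields, after confirming that those fields are in the requested extract. The timeline already sets aside months 0–9 for the data application and revision of the analysis plan. The price is slightly fewer operations per month and results that apply to a narrower population.
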